### Depressive symptoms

The Hamilton Depression Rating Scale (HDRS) is used to measure depressive symptoms as the primary outcome. A large number of studies have shown it to be a valid and reliable measure of depression [34]. Also it is sensitive to changes due to drug effects in a general practice setting [35]. The structured 17-item interview version of the HDRS is being used in this study and all the researchers involved have received extensive and on-going training in this measure [36]. Inter-rater reliability of ratings on the HDRS is being assessed at intervals throughout the recruitment and follow-up period.

The Beck Depression Inventory second edition (BDI-II) is a second measure of depressive symptoms [37]. This is a 21-item self-report rating inventory measuring characteristic attitudes and symptoms of depression. As this is self-complete it should be essentially free of any observer bias which will enable a check to be carried out to ensure that there is no systematic bias in the HDRS ratings arising from possible un-blinding of the researchers to treatment arm.

### Quality of life

The SF-36 is a questionnaire consisting of 36 items concerning respondents' health-related quality of life [38]. The responses to the items can be condensed into scores on eight domains of health-related quality of life: physical functioning, role-physical, role-emotional, social functioning, pain vitality, mental health and general health. The SF-36 will be used to calculate quality-adjusted life years (QALYs) to be used in the cost-effectiveness or cost utility analysis.

### Short life events and difficulties scale

This instrument is usually used to collect information about stressful experiences over a one-year period before onset/relapse of disorder. It differs from many other stress measures by distinguishing acute from ongoing stressors (events from difficulties), and by contrasting short and long term, and contextual and subjective ratings of these experiences. Specific qualitative aspects of stress such as losses, dangers, humiliations, entrapments, challenges and goal frustrations are also deliberately contrasted [39]. The shortened version of the LEDS, used in this study, is essentially the same interview process but the ratings concentrate on those events that are considered severe, with marked or moderate threat to the individual, and not on those which are deemed to carry only some or little threat, unless they are a fresh start experience of the type found to predict depressive remission.

### Alcohol consumption

The Alcohol Use Disorders Identification Test (AUDIT) is a 10-item questionnaire designed by the World Health Organisation to screen for hazardous alcohol intake in primary health care settings. It has high sensitivity and specificity and can be self-completed or administered in 2–4 minutes [40].

### Somatic symptoms

The Bradford Somatic Inventory is a 46 item questionnaire about symptoms experienced in the last month, which was especially designed to detect physical symptoms commonly found in depressed patients [33].

### Patient satisfaction

This is a 7-point Likert rating scale to determine the patient's satisfaction with the care they have been given. This includes the doctor's explanation of the illness and its seriousness, whether the doctor told the patient what they wanted to know, the doctor's interest in the person, warmth, friendliness, treatment of the patient as an equal, understanding, relief of problems relief of worries, and whether the patient understood how to follow the doctor's advice. This questionnaire was developed by the Primary Medical Care Group at Southampton.

### Care received

This is being measured at 12 and 26 weeks using a self-report questionnaire that was specifically designed for this study to provide a measure of the content of the consultations in order to determine whether supportive care was comparable in both arms. It includes 4 questions devised by Morisky et al [41] which are used to measure patient adherence to the medication for those in the antidepressant treatment arm.

### Economic evaluation

#### Client Service Receipt Inventory

Service use is measured comprehensively using a modified version of the Client Service Receipt Inventory (CSRI) [42] at baseline and 26 weeks. This will allow the economic impact of the different treatment options to be ascertained. Services measured include all contacts with GPs, other primary care professionals, psychiatrists, psychologists, community mental health nurses, counsellors, social care professionals and complementary therapy.

#### Analysis of costs

Costs are calculated using data collected through the CSRI at the 12 and 26 week follow ups. Service use and medication data which are collected from the surgery records will be pooled with the CSRI data to maximise completeness. These will be multiplied by standard unit cost data to generate service costs for each patient.

### Sample size

The sample will be divided into two severity sub-groups (HDRS scores 12–15 and 16–19). Hollyman *et al *found the standard deviation (SD) of the HDRS to be around 3.5, and reported roughly similar numbers of patients in these two severity ranges [43]. We assume this SD, equal numbers in the two sub-groups, a pre-post correlation of 0.5, and significance level of 0.05.

Using analysis of covariance controlling for baseline values, 49 patients at follow-up in each treatment/severity combination will allow the following effects to be detected (standard effect sizes in brackets): an overall average difference in HDRS score of 1.4 (0.4) with 90% power; an interaction (difference between effects in the two severity sub-groups) of 2.5 (0.7) with 80% power; and a difference between treatment arms within the more severe group of 2.0 (0.6) with 90% power. The latter two calculations are conservative (tending to underestimate the power) because the SDs may be lower within the severity subgroups. A difference of 1.4 on the HDRS is a relatively small difference (0.4 standard deviations) and any difference smaller than this we regard as clinically insignificant. In the trial of amitriptyline by Hollyman *et al *the HDRS scores fell by a mean of around 10 points in the mildly depressed group and around 13 in the more severely affected group [43]. Therefore the sample size should be sufficient to detect clinically significant differences.

One hundred and ninety six patients will therefore need to be followed up to detect these differences (98 in each of the two arms). To allow for up to 25% loss to follow-up at 12 weeks, 261, 87 at each of the three sites, would be needed. The aim is to recruit 300, 100 at each site.

### Analysis

Analysis of covariance, controlling for baseline value, severity sub-group and centre will be used to estimate the overall treatment effectiveness (difference in HDRS score) at follow up. The primary analysis will be by 'intention to treat' using double sided tests. The interaction between severity sub-group and treatment will be tested, and if appropriate, effects within separate severity sub-groups estimated. Further exploratory analyses will also assess the impact of other explanatory factors and will also model the time course of effects using the 12-week measurement in a panel analysis. Sensitivity analyses will include estimating 'on treatment' effects and CACE (complier average causal effects), and by imputation of any missing values.

The main aim of the economic analysis is to compare the two treatment groups in terms of mean costs and cost-effectiveness. A secondary aim is to examine differences between the sub-groups defined by severity. Cost data are frequently skewed and this can cause a violation of the assumptions of standard significance tests. In the event of this, bootstrapped estimates (multiple re-sampling within treatment arms) will be determined, whereby mean costs can still be compared whilst imposing no prior assumptions regarding the data distribution. To explore cost-effectiveness, a net benefit variable will be generated which synthesises data on costs and outcomes, also analysed by bootstrapping.

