### Randomisation

Block randomisation with random block sizes, stratified by severity sub-group and centre, is carried out by an independent centre (The Institute of Psychiatry Clinical Trials Unit) over the telephone.

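### The cost and net-benefit comparisons name no covariates, although baseline service use and the randomisation strata are available and the HDRS analysis is adjusted

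*Protocol article*

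**What the plan says.** All references are to the protocol article.

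- **Clinical outcome (Analysis):** "Analysis of covariance, controlling for baseline value, severity sub-group and centre will be used to estimate the overall treatment effectiveness".
- **Economic aim (Analysis):** "The main aim of the economic analysis is to compare the two treatment groups in terms of mean costs and cost-effectiveness". Differences between the severity sub-groups are a secondary economic aim.
- **Costs (Analysis):** should skewness make the usual tests unreliable, then "bootstrapped estimates (multiple re-sampling within treatment arms) will be determined, whereby mean costs can still be compared". The bootstrap of costs is therefore conditional on skewness. Otherwise standard tests apply.
- **Net benefit (Analysis):** "a net benefit variable will be generated which synthesises data on costs and outcomes, also analysed by bootstrapping". No condition is attached here.
- **Data available:** service use is recorded with the "Client Service Receipt Inventory (CSRI) [42] at baseline and 26 weeks" (Client Service Receipt Inventory). Allocation is "stratified by severity sub-group and centre" (Randomisation).
- **QALYs (Quality of life):** these are derived from the SF-36. Table 1 should show when the SF-36 is collected, but its cells are blank in the text at hand.

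No covariate is named for costs, QALYs or net benefit, and none is ruled out.

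**The concern.** The same section treats the two halves of the first research question differently. For HDRS it states a covariate-adjusted model. For costs and net benefit it states the comparison (arm means), the re-sampling (within arm) and the reason (no distributional assumption). Together these describe an unadjusted two-sample contrast. The standard tests used when costs are not too skewed come without covariates as well.

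What is at stake is efficiency. The Sample size section gives no power for any economic comparison, so precision there is whatever the analysis delivers. Earlier service use plausibly predicts later service use, and centres may differ in it. Leaving these out means wider intervals than the data require. A chance difference at baseline also stays in the estimate. For QALYs part of this is mechanical: if baseline utility is one of the points under the curve, any baseline difference enters the QALY difference directly.

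**Working it through.** **1. What baseline adjustment is worth in the plan's own figures.** There is no stated figure for the economic comparison, so the HDRS figure serves as the check. Inputs from Sample size: SD 3.5, pre-post correlation 0.5, 98 per arm, difference 1.4, significance level 0.05, two-sided.

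- Residual SD = 3.5 × √(1 − 0.5²) = 3.031.
- SE = 3.031 × √(2/98) = 0.433. Then 1.4/0.433 = 3.233, and power = Φ(3.233 − 1.960) = 89.9%. The stated 90% is reproduced.
- Without the baseline covariate: SE = 3.5 × √(2/98) = 0.5. Then 1.4/0.5 = 2.8, and power = Φ(2.8 − 1.960) = about 80%.

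So the plan already relies on baseline adjustment for HDRS. The correlation of 0.5 is an HDRS figure and cannot be carried over to costs.

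**2. Costs and net benefit.** With correlation r between baseline covariate and outcome, the variance of the arm difference is multiplied by 1 − r² and the interval width by √(1 − r²). The documents give no r for costs, so these values are assumptions.

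| Assumed r | Variance factor | Interval width relative to unadjusted |
|---|---|---|
| 0.1 | 0.99 | 0.995 |
| 0.3 | 0.91 | 0.954 |
| 0.5 | 0.75 | 0.866 |
| 0.6 | 0.64 | 0.800 |
| 0.7 | 0.51 | 0.714 |

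At r of 0.3 to 0.6, intervals are about 5 to 20% narrower.

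**3. Skewed costs.** A simulation used log-normal costs (log-scale SD 0.9), no treatment effect, 98 per arm and 600 runs, with 300 within-arm re-samples each. It included a baseline cost but no strata.

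| Log-scale correlation | SD of estimate, unadjusted | SD of estimate, adjusted | Reduction | Coverage, unadjusted | Coverage, adjusted |
|---|---|---|---|---|---|
| 0.3 | 73.0 | 70.8 | 3% | 93.5% | 93.2% |
| 0.5 | 71.1 | 65.2 | 8% | 93.7% | 93.0% |
| 0.7 | 73.5 | 53.2 | 28% | 93.0% | 96.2% |

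The mean unadjusted estimate was −2, −1 and +5 against a true value of 0. The Monte Carlo standard error of that mean is about 72/√600 = 2.9, so there is no evidence of bias. For coverage the Monte Carlo standard error near 95% is √(0.95 × 0.05/600) = 0.9 percentage points.

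The gains at 0.3 and 0.5 are smaller than in step 2 because skewness lowers the correlation on the cost scale. For log-normal costs it is (e^(0.81r) − 1)/(e^0.81 − 1), where 0.81 = 0.9². Log-scale 0.3 and 0.5 become 0.22 and 0.40, giving width factors of 0.975 and 0.917, in line with the simulation. Log-scale 0.7 becomes 0.61, with a factor of 0.79. The simulated 28% lies somewhat above the 21% this implies, so it should be read as approximate.

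**4. QALYs.** Assume utility at 0, 12 and 26 weeks and the trapezoid rule. The baseline weight is (12/52)/2 = 0.115 of a total of 0.5 years; the later weights are 0.250 and 0.135. Each 0.01 difference in baseline utility therefore moves the QALY difference by about 0.0012. Assume further a utility SD of 0.10 to 0.20:

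- SE of the baseline difference with 98 per arm = SD × √(2/98) = 0.0143 to 0.0286.
- Direct shift from an imbalance of one SE = 0.115 × SE = 0.0016 to 0.0033 QALY.
- If later utilities also correlate 0.5 with baseline: (0.115 + 0.5 × 0.385) × SE = 0.0044 to 0.0088 QALY.

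**The case against.** The strongest reply is that this is a condensed article. Covariates of an economic model are commonly left to the full plan, and silence is not exclusion. Re-sampling within arms says how patients are drawn, not which estimator is applied to each draw, so a bootstrapped regression fits the wording. This stands in part: the text contains no error or contradiction on this point. But the paragraph does set out its method, and beside an explicitly adjusted HDRS model it reads most naturally as unadjusted.

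A reader might infer more, and the documents do not support it:

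- **That raw arm means are the fixed method and covariates are excluded.** The text does not say so, and the cost bootstrap applies only if skewness requires it.
- **That the baseline CSRI will go unused.** No use is stated, but none is ruled out.
- **That the result would be biased, or its intervals invalid because allocation was stratified.** Randomisation makes the unadjusted contrast unbiased on average, and simulated coverage was 93 to 94%. The simulation did not model the strata, so it does not test that aspect, but nothing shows harm to coverage.
- **That baseline SF-36 data are in hand.** This cannot be confirmed with Table 1 blank.
- **That severity is ignored.** It enters the economics as a secondary sub-group aim.

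It is also fair to say that the size of the gain rests on correlations that the documents do not give, and that no change in a cost-effectiveness conclusion has been shown.

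**Conclusion.** The point holds as a modest recommendation. No adjustment is named for costs, QALYs or net benefit, while baseline service use, severity sub-group and centre are available. An unadjusted analysis would be valid but would give up precision and leave the estimates open to chance imbalance.

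The size is not determinable from the documents. It is about 5 to 20% in interval width if baseline and follow-up cost correlate 0.3 to 0.6. In the skewed-cost simulation it is about 3% and 8% at log-scale correlations of 0.3 and 0.5. Any further gain from severity and centre has not been quantified. The QALY shifts depend on assumed utility SDs and an assumed SF-36 schedule.

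**What to change.** State in the economic part of Analysis that costs, QALYs and net benefit are each estimated by bootstrapped regression on treatment arm, with baseline CSRI cost, severity sub-group and centre as covariates. For QALYs and net benefit, add baseline SF-36 utility if the SF-36 is collected at baseline. Re-sample each patient's costs and outcomes together, within arm. Fix the covariates before cost data are seen by arm, so that they cannot be chosen on the results.

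The cost is a sentence or two of wording, the costing of the baseline CSRI and slightly more programming. The cost adjustment needs no new data.

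While editing, reconcile the CSRI time points. The Client Service Receipt Inventory section places it "at baseline and 26 weeks", whereas Analysis of costs draws on the 12- and 26-week follow-ups.

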## Discussion

It is intended that this study will provide the evidence needed to enable GPs to decide which of their patients suffering from mild and moderate depression are most likely to benefit from taking an SSRI antidepressant with regard to severity as well as other predictors.
